### Randomisation

A total of 47 facilities, 23 in Bamenda and 24 in Yaoundé, will be randomised within stratum to receive current practice, the basic intervention (RDTs and basic training) or the enhanced intervention (RDTs with enhanced training). With cluster randomised trials there is an increased chance that the study arms are unbalanced with respect to known and unknown potential confounders, and therefore undermines the credibility of the trial results. Stratified randomisation will reduce the likely imbalance in factors known to be correlated with the study outcome and the study site. However, the current availability of microscopy and the type of facility (which will also capture variation in health worker and patient characteristics) were assumed to be important correlates and therefore a process of constrained, or restricted, randomisation [34,35] will also be implemented to balance these two factors across the study arms using data collected in the formative research.

Using restricted randomisation schemes increases the risk of producing a design which is biased and not valid. Moulton [35] describes a design as being biased if there is any difference across the clusters in their probability of allocation to any given treatment. A randomised design is said to be valid if every pair of clusters has the same probability of being allocated to the same treatment. If the design is not valid there is a risk that the Type I error changes from its nominal value of 0.05. We will assess the validity of the restricted randomisation by producing a matrix where the rows and columns represent the clusters and the elements of the matrix are the proportion of times each pair of clusters is allocated to the same study arm i.e. the probability that the i^th ^cluster is being allocated to the same intervention group as the j^th ^cluster. The matrix will then be examined for under- and over-represented pairs that would highlight any potential causes for concern in the randomisation.

Randomisation of the facilities will be performed by the study statistician after informed consent has been sought from the head of the facility to avoid selection bias. Patients (or caregivers) and fieldworkers administering the patient exit survey will be blinded to group assignment. The research team involved in implementing the training interventions and supervising data collection will need to be aware of which facilities receive the different interventions.

Figure 3 shows study eligibility, selection, enrolment and methods of data collection.

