#### Control Arm

The control arm represents current practice. Providers in these facilities will not receive RDTs or training as part of the study and are expected to continue to provide usual medical care for fever patients attending their facility. Our formative research showed that 90% of public health facilities and all mission health facilities in the study sites had microscopy testing, though none had RDTs.

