#### Patient exit survey

The primary outcome will be measured through an interviewer-administered patient exit survey. Data collection will commence three months after the intervention has been implemented. The three-month lag in the data collection is to ensure that the effect measure reflects treatment practices in the medium-term. In the short-term it is recognised that it is possible that the effect is overstated because health workers may change practices initially but revert to past behaviours over time, or that the effect is understated because it takes time for the training to have an effect as some health workers are hesitant and want to learn from the experience of the early-adopters. The survey data collection will take up to two months and will be organized such that the data will show the effect of the intervention over this time period by establishing a maximum number of patients that can be surveyed each week.

The research team will recruit field workers and provide training over a week on all aspects of data collection related to the patient exit survey. The training will include a practical assessment of their ability to provide information to respondents about the survey, obtain consent and administer the questionnaire. The research team will supervise the field workers and will accompany the field worker at the start of data collection to obtain consent from the head of the facility and ensure the fieldworker adheres to the standard operating procedures. Supervisory visits to monitor the performance of the field workers will take place at least once each week during the data collection period.

The patient exit questionnaire is designed to collect information about the patient's experience of seeking treatment and has been piloted a selected facilities in the study site. The questionnaire contains the following ten modules:

A. Background Information, Consent and Screening Questions

B. Details of the Respondent and/or Patient

C. Reasons for attendance

D. Consultation and diagnosis

E. Treatment prescribed and received

F. Patient satisfaction and knowledge of malaria

G. Costs of seeking treatment

H. Household characteristics

I. Malaria test completed by the study team (in sub-sample of patients)

J. Malaria test completed by health workers (from register of malaria tests at facility)

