#### Register of malaria tests conducted

The patient exit questionnaire will be supplemented by a register of malaria tests at each participating health facility because patients may not always know if they were tested for malaria and the result of the malaria test. With consent from the head of the facility, health workers responsible for conducting malaria tests will be asked to keep a register of all malaria tests undertaken. The following data will be collected: details of the patient, availability of microscopy and RDT, method of test conducted, test result and the provider that conducted the test. At each facility the field workers will collect the register of malaria tests at least once each week and will use the patient's name, gender, age, date of visit to identify the patients that completed the survey and record the details in Section J of the questionnaire.

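### Exit-survey fieldworkers are declared blinded, but the test register that field workers collect and transcribe lets them infer which facilities are control and which have RDTs

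*Protocol article*

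**What the plan says.** The blinding claim is in the protocol article under Randomisation: "Patients (or caregivers) and fieldworkers administering the patient exit survey will be blinded to group assignment". The same section separates these people from the research team who run the training and supervise data collection, and who are acknowledged to need the allocation.

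The field procedure is described in two places.

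- **Patient exit survey.** The research team recruits field workers and will "provide training over a week on all aspects of data collection related to the patient exit survey". The survey is interviewer-administered and is the source of the primary outcome. Its ten modules include D (consultation and diagnosis), E (treatment) and "J. Malaria test completed by health workers (from register of malaria tests at facility".
- **Register of malaria tests conducted.** Health workers keep a register holding "details of the patient, availability of microscopy and RDT, method of test conducted, test result and the provider that conducted the test". Then, "At each facility the field workers will collect the register of malaria tests at least once each week". The field workers link entries to surveyed patients by name, gender, age and visit date, and "record the details in Section J of the questionnaire".

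On who has RDTs, Supply of RDTs gives them to both intervention arms. Control Arm gives none to control facilities and reports that at formative research the facilities had microscopy, "though none had RDTs". Study area and participants makes facilities in the Government's RDT pilot ineligible.

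**The concern.** The register contains a field that, in this trial, almost coincides with the control versus intervention contrast. The group of staff declared blind handles that register every week at every facility. A masking statement and a procedure that undoes it for two of the three primary comparisons cannot both stand as written.

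The primary outcome depends on information these staff collect or link. It is a composite of whether the patient was tested, what the result was, and whether the treatment received fits the result. Answers given in an interview can be influenced by an interviewer who has a view about the facility. The register is used because patients may not know whether they were tested or what the result was, so the link between a register row and a patient also feeds the outcome. A reader of the trial report would credit the comparisons with control with assessor blinding that the procedures do not secure.

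**Working it through.** No figure in the plan is at issue, and no sample size, power or margin enters. The check is a comparison of the sections.

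1. **Are the blinded staff and the register staff the same group?** Randomisation refers to the fieldworkers who administer the exit survey. Patient exit survey and Register of malaria tests conducted both use the term field workers, and Section J, filled from the register, is a module of the exit questionnaire. No separate register staff are described. The article supports one staff group doing both tasks.

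2. **Does the register reveal RDT status?** Yes, through two fields: availability of RDTs and method of test. The availability field matters because it would mark an intervention facility even where providers mostly went on using microscopy.

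3. **Does RDT status reveal the arm?** Intervention facilities are supplied by the study, with a supply intended to be stable. Control facilities are not supplied, none had RDTs in the formative research, and Government pilot facilities are excluded. RDT entries therefore point to an intervention facility, and a run of entries without them points to control.

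4. **When does this become possible?** At the latest from the first register collection, so interviews in later weeks are exposed. Module D may reveal RDT use before that. Field workers are also familiar with RDTs, because under Independent verification they perform them in a 5% sub-sample of patients who reported a test.

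5. **Which comparisons are affected?**

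| Comparison | RDTs supplied by the study | Distinguishable through the register? |
|---|---|---|
| Basic v control | Basic yes, control no | Yes |
| Enhanced v control | Enhanced yes, control no | Yes |
| Enhanced v basic | Both yes | No |

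The first two are primary objectives. The third, which drives the 19 clusters per intervention arm, is not unmasked by this route.

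**The case against.** The strongest reply is that blinded may simply mean not told. The register has the same layout at every facility, and a field worker must also know that RDT presence marks the arm. The article does not say whether their training discloses the design. The finding that no facility had RDTs comes from formative research, not from the trial period. All of this stands to the extent that allocation is inferred rather than disclosed. It does not rescue the statement, because the inference is easy and the article describes nothing to prevent it.

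A second reply points to the safeguards: a quality assurance officer, standard procedures, weekly review of questionnaires, double entry, comparison of patient report with the register, independent RDTs in the 5% sub-sample, and PCR in a sample. These protect the accuracy of test data and data entry. None of them restores masking or checks for interviewing or matching that differs by arm.

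Three stronger readings are tempting, and the documents do not support them.

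- *Unblinding is complete.* The documents show that arm status can readily be inferred, not that every field worker knows it.
- *The same individual interviews a patient and decides which register row is theirs.* The article speaks of field workers collectively and does not assign both tasks for one patient to one person. Test entries are written by health workers, and four identifiers limit the discretion in matching.
- *A few doubtful matches would shift the result by a known amount.* One might reason that 3 patients in 100 is 3 points, or 3/15 = one fifth of the 15-point target. Because the outcome is composite, a patient reclassified as tested counts only if treatment also fits the result, so 3 points is an upper limit for 3 changed records. Nothing in the article indicates that such errors occur or that they run in one direction at every facility.

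**Conclusion.** The point holds in a limited form. The article claims fieldworker blinding without qualification and specifies a procedure through which control versus RDT status can readily be inferred. Masking is therefore not secured for basic versus control or enhanced versus control, while basic versus enhanced is untouched by this route. The direction and size of any bias cannot be derived from the document.

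This rests on three assumptions: field workers in the two sections are the same staff group, as the shared term and questionnaire indicate; control facilities remained without RDTs during the trial; and nothing outside the article kept staff unaware that RDTs were part of the intervention. It is not a matter that an analysis plan could settle, since the conflict lies between a design statement and a field procedure.

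**What to change.** 1. **Restate the blinding.** Say that fieldworkers and patients are not told the allocation, that masking can be expected only for basic versus enhanced, and that the comparisons with control should be treated as not assessor-blinded. This costs only wording.

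2. **Protect the matching.** Link register entries to patients on name, gender, age and visit date, with sections D and E out of view. Where existing staffing allows, have this done by a field worker who did not interview at that facility, or after that facility's interviews end. Completing the interview sections before opening the register would add little: with exit interviews and roughly weekly register collection this largely happens already, and it cannot re-mask interviews in later weeks.

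3. **Report a sensitivity analysis** of the primary outcome using patient-reported testing alone. It removes the influence of register matching but not that of the interviewer, and some patients will not know their result. The full analysis plan is not shown, so its absence from the article is not a fault.

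The downside is a small change in field procedure partway through data collection, since Trial status says exit-survey recruitment is already under way. Records matched before the change should be identifiable, and the masking actually achieved should be reported.

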**Figure 3 F3:**
[figure not shown]
**Eligibility, selection, enrolment and methods of data collection**.

### Data analysis

Initially an overall test of the null hypothesis that there are no differences between either of the intervention arms and the control will be performed to guard against over-interpretation of any significant effects from individual comparisons of each intervention with the control, particularly if there is no evidence of a difference for any of the intervention arms.

The effect of the two interventions compared with control will be analysed with methods appropriate for cluster randomised trials. Point estimates of the primary outcome will be calculated using the unweighted mean of the cluster summaries in each stratum. If the distribution of the summary measures in each study arm is skewed, a logarithmic transformation to the proportions will be considered. An overall estimate of the risk ratio will be obtained by taking a weighted average of the stratum-specific risk ratios where the weights are inversely proportional to the stratum-specific variances. 95% confidence intervals (CI) will be adjusted for observed between-cluster variance and formal hypothesis testing will be conducted using stratified t-tests. Adjustment for covariates, including patient and provider characteristics and knowledge, contextual factors and process factors, will be carried out using a two-stage process. In the first stage, a logistic regression model including stratum as a fixed effect and the covariates of interest, but excluding the intervention effect, will be fitted to calculate cluster-specific expected values. The ratio of observed and expected values will be computed to give the ratio-residual for each cluster. In the second stage, the above methods for estimating the RR and 95% CI and hypothesis testing are carried out with the cluster-level proportions replaced with the covariate-adjusted residuals [35].

Non-inferiority between the two intervention arms will be assessed using the same methods as described above but instead of the risk ratio the risk difference will be estimated. Inference will be based solely on one-sided 95% CIs (or equivalently 2-sided 90% CIs).

Secondary outcomes on treatment received by patients, and provider knowledge and practice, will be analysed using the methods described above. To examine whether secondary outcomes vary according to the urban/rural residence and socioeconomic status of the patients methods appropriate for examining an interaction between the intervention and the individual-level variable will be applied [36]. Differences in coverage estimates between the intervention arms will also be estimated by calculating the arithmetic mean of the coverage proportions in each cluster and conducting a two-way analysis of variance, allowing for stratification.

For the economic analysis, cost-effectiveness ratios will be based on the primary outcome (i.e. the cost per case of suspected malaria that received treatment as recommended in the malaria guidelines) as well as a range of secondary outcomes including changes in provider knowledge. Cost-effectiveness will be calculated for each comparison and will be expressed as incremental cost-effectiveness ratios (ICERs). One-way and multi-way sensitivity analysis will be undertaken to examine the effects of varying uncertain variables on study findings. Costs and effects will be presented in both discounted and undiscounted form.

All data will be double entered using Microsoft Access 2007 (Microsoft Inc., Redmond, Washington) and analysed using STATA version 11.0 (STATA Corporation, College Station, Texas). A full analysis plan will be reviewed and agreed before the data are analysed.

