#### Basic Provider Training (BT)

Facilities randomised to the basic intervention will be supplied RDTs and receive basic provider training on malaria diagnosis and treatment. This training is intended to mimic the style of workshop that is routinely implemented as in-service health worker training. The training will be conducted over one day and contain three training modules: 1) Malaria Diagnosis; 2) Rapid Diagnostic Testing; 3) Malaria Treatment. Together these three training modules will provide health workers with the knowledge and skills on why malaria testing is recommended, how to use an RDT, the treatment algorithm and details contained in the malaria guidelines. The malaria guidelines state how confirmed cases of uncomplicated malaria should be treated, including advice on dosing and treatment regimens for different types of ACT. The training also provides advice on other causes of febrile illness which should be investigated if the malaria test is negative. The module on RDTs includes a practical session in which all health workers will get hands-on experience of the steps involved in using an RDT.

The training will be conducted in conference halls of health districts located in both study sites. The following types of providers will be invited to the training: medical doctors, nurses, laboratory technicians and pharmacy attendants. Each facility will be invited to select 3 providers to attend the training. The training will be conducted jointly by medical doctors, representatives of the national malaria control programme and the research team. The trainers will receive extensive briefing by the research team and given a trainer's manual which provides detail of the material for each module and how it should be delivered. The training manual also includes standardized power-point presentations. In addition, the trainers will be trained in presentation and communications skills.

Each basic training workshop will train 25-30 providers. The training primarily takes a didactic seminar style in which the trainer delivers the training material, though there is scope for questions and discussion. A participant's training manual will be given to providers that attend the training course and includes all essential reference material including the malaria treatment guidelines. Participants will also be provided with job aids for RDTs and a treatment algorithm to be placed on their tables while in their health facilities.

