#### Secondary outcomes

Secondary outcomes include:

• Proportion of febrile patients that are tested for malaria

• Proportion of febrile patients receiving an antimalarial that receive an ACT

• Proportion of febrile patients receiving an ACT that receive the correct dose for their age

• Proportion of febrile patients receiving an ACT that accurately report how to take the medicine

• Proportion of febrile patients that report they are satisfied with the care received

• Proportion of HWs that report they were satisfied with the training received

• Proportion of HWs that know ACT should be given if the malaria test is positive and that an antimalarial should not be given if the malaria test is negative

• Proportion of HWs that report febrile patients should be tested for malaria

• Proportion of HWs that know how to identify positive, negative and invalid malaria RDT results

• Proportion of HWs that know the correct dose of the first-line ACT in an adult and in a child aged 2 years

• Total cost of the provider interventions and the cost per HW attending the BT and ET

Secondary outcomes related to patients will also be reported in terms of their urban/rural residence and socioeconomic status.

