### Evaluation design

The evaluation of the intervention will use data collected in a patient exit survey, a register of malaria tests conducted by the provider during patient consultations, a provider survey, documentation of the intervention process, costing of the intervention activities and lastly, independent testing of malaria by the study team (see 'quality assurance'). The patient exit survey will be administered before the provider survey to ensure that the treatment received by patients is not influenced by the content of the provider questionnaire. Each of these is described below.

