#### Documentation of the Intervention Process

The implementation of the malaria training workshops delivered to health workers will be documented. Details of all participants attending the training course will be recorded. Participants will undertake a pre- and post-training test to determine the impact of the training on their knowledge of malaria diagnosis and treatment. All participants will be invited to complete the training evaluation, which assesses the content and delivery of the training course. In addition, the trainers will complete a form to record any challenges faced in running the training workshop. Finally, the process of distributing the RDTs to health facilities will be monitored and any problems with the procedures for replenishing RDT stocks will be documented.

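### The covariate-adjusted analysis includes provider knowledge and process factors, which the intervention can change, so its risk ratio is pulled towards 1 wherever those factors differ by arm

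*Protocol article*

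**What the plan says.** The Data analysis section first sets out an analysis without covariates: unweighted cluster means by stratum, a weighted risk ratio, cluster-adjusted confidence intervals and stratified t-tests. It then adds: "Adjustment for covariates, including patient and provider characteristics and knowledge, contextual factors and process factors, will be carried out using a two-stage process".

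Stage 1 is a logistic model with stratum and the covariates, "but excluding the intervention effect, will be fitted to calculate cluster-specific expected values". The ratio of observed to expected is taken for each cluster. In stage 2 the risk ratio, its interval and "hypothesis testing are carried out with the cluster-level proportions replaced with the covariate-adjusted residuals". The section neither limits the covariates to values fixed before randomisation nor labels the analysis as explanatory or mediational.

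Other sections show where knowledge stands in the trial:
- **Basic Provider Training (BT):** "Together these three training modules will provide health workers with the knowledge and skills on why malaria testing is recommended". The enhanced training contains the same modules.
- **Secondary outcomes:** the list includes "Proportion of HWs that know ACT should be given if the malaria test is positive".
- **Patient exit survey:** "Data collection will commence three months after the intervention has been implemented".
- **Evaluation design:** "The patient exit survey will be administered before the provider survey".
- **Documentation of the Intervention Process:** "Participants will undertake a pre- and post-training test to determine the impact of the training on their knowledge of malaria diagnosis and treatment". The same section describes recording workshop attendance and delivery, and monitoring RDT distribution.
- **Control Arm:** these facilities get neither RDTs nor training from the study.

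**The concern.** An adjusted estimate of an intervention effect should condition only on things that the intervention cannot have changed. Provider knowledge is one of the routes by which training is meant to work, and the trial also counts it as a result. Process measures such as share of staff trained or RDT supply are consequences of allocation and are close to a label for arm.

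Leaving arm out of stage 1 is sound for baseline covariates, because randomisation balances them in expectation. For a covariate that allocation has shifted, the stage 1 coefficient picks up the difference between arms, whether or not the covariate causes anything. Expected values then rise in the trained arms and fall in control, and the observed-to-expected ratios draw together.

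At stake is the meaning of the adjusted risk ratio. It would be reported with an interval and a test, yet it would answer a different question from the stated objective. The Data analysis section also applies its methods to provider knowledge outcomes, where adjusting for knowledge would be circular.

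**Working it through.** The plan states no figure for the adjusted estimate, so there is none to reproduce. The check has four steps.

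**1. When each covariate is known.** The provider survey follows the exit survey, which starts three months after the intervention. It is the only knowledge measure described for providers in all arms. The pre-training test covers workshop participants only, so it gives no control baseline. If "knowledge" also means patients' knowledge, that comes from module F of the same post-intervention exit survey.

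**2. The mechanism by hand.** Take the planned 15% v 30% with 9 control and 19 intervention facilities of equal size (Sample size section).
- Covariate balanced across arms: the mean expected risk in both arms is the pooled risk, (9 × 15 + 19 × 30)/28 = 705/28 = 25.18%. Observed/expected is 15/25.18 = 0.596 in control and 30/25.18 = 1.191 with intervention. The ratio is 1.191/0.596 = 2.0, so nothing is lost.
- Covariate that coincides with arm: the fitted means are 15% and 30%, observed/expected averages 1 in each arm, and the ratio is 1. The whole effect is removed.

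Real covariates fall between these limits, at a point set by how far they differ by arm.

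**3. What the plan says about the knowledge gap.** It gives no expected difference. The Provider survey part of the Sample size section assumes 90% knowing the guidelines in each arm, control included. With 9 facilities, 3.5 providers each and ICC 0.1, the half-width is 1.96 × √[p(1 − p)/31.5 × (1 + 2.5 × 0.1)].
- p = 0.90: 1.96 × √(0.09/31.5 × 1.25) = 11.7%, against the stated 11.8%.
- p = 0.50: 1.96 × √(0.25/31.5 × 1.25) = 19.5%.

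So the stated control precision does rest on 90%. It is a precision input, not a forecast of the gap.

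**4. Simulation of the two-stage method.** Settings: 9 v 19 facilities, 100 patients each, 15% v 30%, stage 1 with stratum and the covariate but not arm, stage 2 on observed/expected ratios, 200 to 400 runs per setting. Knowledge levels and within-arm associations are assumptions.

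| Covariate in stage 1 | Knowledge, control v trained | Adjusted risk ratio |
|---|---|---|
| None, or stratum only | any | 1.90 to 1.99 |
| Knowledge | 90% v 90% | 1.98 to 2.01 (unadjusted 2.01 to 2.07) |
| Knowledge | 85% v 90% | 1.83 to 1.97 (unadjusted 2.00 to 2.05) |
| Knowledge | 70% v 90% | about 1.6 to 1.9 |
| Knowledge | 50% v 90% | about 1.2 to 1.7 |
| Share of staff trained (0 in control, assumed mean 70% in trained) | not used | 1.16 to 1.19 |

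The spread within a row reflects whether knowledge is scored by facility or by patient and how strongly it is tied to the outcome within arm. A further set of runs varied the share of the effect that passes through knowledge. With knowledge at 40% v 60%, 75% and 90%, the adjusted risk ratio was 1.65, 1.38 and 1.19 when none of the effect passed through knowledge, and about 1.0 in all three when all of it did. The first three figures show that attenuation needs no causal role for the covariate.

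For enhanced v basic at 30% v 40%, 19 facilities per arm and 90% knowledge in both, the risk ratio moved only from 1.32–1.33 to 1.30–1.32.

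**The case against.** Four points can be made on the other side.

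- **The first-described analysis is complete without these covariates.** This stands. Nothing says that the adjusted result is primary or replaces it. A reader might infer that the trial's main effect estimate is biased; the text does not support that.
- **The attenuation could be negligible.** This stands as to size. A reader might infer that the adjusted risk ratio must be heavily attenuated. That follows only from an assumed large gap, and the one planning figure in the article is 90% in every arm.
- **Non-inferiority may be untouched.** This largely stands. A reader might infer that the comparison of enhanced with basic is tilted towards non-inferiority. The section says that the same methods apply, but on the risk difference, whereas the adjustment described is a ratio-residual built for the risk ratio. Both trained arms also share the three knowledge modules. Bias towards no difference arises only if the adjustment is used there and these factors differ between the two arms.
- **The term is loose and a full analysis plan is promised.** Process factors are not defined, and reading them as training delivery and RDT supply is an inference from the process documentation. The later plan could narrow the list. This softens the point without removing it, because the article already names knowledge and process factors as covariates in an analysis that yields a risk ratio, an interval and a test.

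**Conclusion.** The point holds for the covariate-adjusted analysis. It names covariates that arise after randomisation and that the intervention can change, in a model that omits arm. Where they differ by arm, the adjusted risk ratio moves towards 1 and does not estimate the effect of the intervention.

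The direction follows from the method; the size is not established by the documents. Against a planned risk ratio of 2, it runs from almost no loss with equal knowledge to about 1.2 with a 50% v 90% gap or a process factor that nearly encodes arm. All gaps other than 90% in every arm are assumptions made for this check. Heavy attenuation, a biased main analysis and a distorted non-inferiority conclusion are each possible readings that go further than the text allows.

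**What to change.** In the Data analysis section, remove knowledge and process factors from the adjustment used to estimate effects. Restrict it to factors fixed before randomisation or not alterable by the intervention. Examples are site, facility type and microscopy availability from the formative data, and patient age and sex. Facility type and microscopy availability are already used in the restricted randomisation.

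Report knowledge and process measures as outcomes, or in a separately labelled exploratory mediation analysis that is not used for effect estimates or for the non-inferiority decision. State the same restriction in the full analysis plan, which the article says will be agreed before the data are analysed.

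The cost is about one sentence of text, with no change to data collection.
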